### 5.1.2 Secondary Endpoints

*Immunogenicity:*

To assess (qualitative and quantitative) immune responses elicited by the different prime-boost regimens:

1. Proportion of volunteers with HIV-1 specific T-cell responses quantified by IFN- $\gamma$  ELISPOT and magnitude of responses
2. Frequency and magnitude of polyfunctional HIV-1 specific CD4+ or CD8+ T-cell responses assessed by Intracellular Cytokine Staining and Polychromatic Flow Cytometry (ICS/PFC) measuring a panel of cytokines, functional and phenotypic markers after stimulation with HIV-1 antigen peptide pools
3. Epitope mapping to determine specificity and breadth of the responses

### 5.1.3 Exploratory Endpoints

*Immunogenicity:*

Additional immunogenicity assessments may include:

1. Binding antibodies to HIV antigens (frequency and magnitude)
2. Neutralizing antibodies to HIV antigens (seropositivity rates and magnitude of antibody titers)
3. Neutralizing antibodies to the Ad35 vector (frequency and magnitude)

Responses may be further characterized to include:

1. Ability of CD8 cells to inhibit HIV replication in a Viral Inhibition Assay (VIA)
2. Capacity of antigen specific T cells to proliferate
3. Flow cytometry to assess markers for memory, exhaustion and activation, and secretion of cytokines other than IFN- $\gamma$ , IL-2 and TNF- $\alpha$
4. Repertoire analysis to assess B cell response

*Serum antibodies against human IL-12:*

1. Proportion of volunteers/vaccine recipients who develop antibodies against human IL-12

*EP Tolerability:*

1. Proportion of volunteers judging the procedure as acceptable

## 5.2 Study Design

The study is a randomized, double-blind placebo-controlled trial.

**Table 5.2-1: Study Design**

|              |                       | Months 0, 1, 2                                             | Month 6                                                     |
|--------------|-----------------------|------------------------------------------------------------|-------------------------------------------------------------|
| Study Groups | N vaccine / placebo   | Prime Vaccine (dosage, delivery)                           | Boost Vaccine (dosage, delivery)                            |
| 1            | 12/3                  | HIV-MAG (3,000mcg) (IM/EP*)                                | Ad35-GRIN/ENV (2x10  vp*** IM**)               |
| 2            | 12/3                  | HIV-MAG (3,000mcg)
+
GENEVAX® IL-12 (100mcg)(IM/EP)  | Ad35-GRIN/ENV (2x10  vp, IM)                   |
| 3            | 12/3                  | HIV-MAG (3,000mcg)
+
GENEVAX® IL-12 (1000mcg)(IM/EP) | Ad35-GRIN/ENV (2x10  vp, IM)                   |
|              |                       | Month 0                                                    | Month 4                                                     |
| 4            | 12/3                  | HIV-MAG (3,000mcg)
+
GENEVAX® IL-12 (1000mcg)(IM/EP) | Ad35-GRIN/ENV (2x10  vp, IM)                   |
| 5            | 12/3                  | Ad35-GRIN/ENV (2x10  vp, IM)                  | HIV-MAG (3,000mcg)
+
GENEVAX® IL-12 (1000mcg) (IM/EP) |
| Total | 75
(60/15) |                                                            |                                                             |

\*IM/EP=intramuscular by *in vivo* electroporation

\*\*IM=intramuscularly

\*\*\* vp=viral particles

### 5.2.1 Duration of the Study

Volunteers will be screened up to 42 days before vaccination and will be followed for 12 months after the initial vaccination. It will take approximately 3 months to enrol 75 volunteers. The anticipated study duration for each volunteer is approximately 13 months from screening through last study visit.

### 5.2.2 Study Population

The study population consists of healthy male or female adults aged 18-50 years at low risk for HIV infection, who are willing to undergo HIV testing, use an effective method of contraception, and who in the opinion of the investigator or designee, understand the study and provide written informed consent.

Approximately 75 volunteers (60 vaccine recipients, 15 placebo recipients) who meet all eligibility criteria will be included in the study. An over-enrolment of up to 10% (up to 83 volunteers total) will be permitted in the study to facilitate rapid enrolment.

### 5.2.3 Inclusion Criteria

1. Healthy male or female, as assessed by a medical history, physical exam, and laboratory tests;
2. At least 18 years of age on the day of screening and has not reached his/her 51st birthday on the day of first vaccination;
3. Willing to comply with the requirements of the protocol and available for follow-up for the planned duration of the study;
4. In the opinion of the Principal Investigator or designee, and based on Assessment of Informed Consent Understanding (AOU) results, has understood the information provided and potential risks linked to vaccination and participation in the trial; written informed consent will be provided by the volunteer before any study-related procedures are performed;
5. Willing to undergo HIV testing, risk reduction counselling, receive HIV test results and committed to maintaining low risk behaviour for the trial duration;
6. If a female of childbearing potential, willing to use an effective non-barrier method of contraception (hormonal contraceptive or intrauterine device [IUD]) from screening until at least 4 months after the last study vaccination;
7. Assessed by the clinic staff as being at “low risk” for HIV infection on the basis of self-reported sexual behaviour within the 12 months prior to enrolment defined as follows:
  - a. Sexually abstinent, or
  - b. Had two or fewer mutually monogamous relationships with partners who did not use illicit drugs, or
  - c. Had two or fewer partners believed to be HIV-uninfected and who did not use illicit drugs (illicit drug use or abuse that includes any injection drugs, methamphetamines [crystal meth], heroin, cocaine, including crack cocaine or chronic marijuana abuse) and with whom he/she regularly used condoms for vaginal and anal intercourse;
8. All female volunteers must be willing to undergo urine pregnancy tests at time points indicated in the Schedule of Procedures (Appendices A, B) and must test negative prior to each study vaccination;
9. All sexually active males (unless anatomically sterile or in a monogamous relationship with a female partner who uses a documented non-barrier method of birth control) must be willing to use an effective method of contraception (such as consistent condom use) from the day of first vaccination until at least 4 months after the last vaccination;
10. Willing to forgo donations of blood or any other tissues during the study and, for those who test HIV-positive due to trial vaccination (vaccine-induced HIV seropositivity), until the anti-HIV antibody titres become undetectable.

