### 5.2.4 Exclusion Criteria

1. Confirmed HIV-1 or HIV-2 infection;
2. Any clinically relevant abnormality on history or examination including history of immunodeficiency or autoimmune disease; use of systemic corticosteroids (the use of topical or inhaled steroids is permitted); immunosuppressive, anti-cancer, anti-tuberculosis or other medications considered significant by the investigator within the previous 6 months;
3. Any clinically significant acute or chronic medical condition that is considered progressive, or in the opinion of the investigator, makes the volunteer unsuitable

- for participation in the study;
4. Reported risky behaviour for HIV infection within 12 months prior to vaccination, as defined by:
    - Unprotected sexual intercourse with a known HIV-infected person, a partner known to be at high risk of HIV infection or a casual partner (i.e., no continuing established relationship)
    - Engaged in sex work
    - Frequent excessive daily alcohol use or frequent binge drinking or chronic marijuana or any other use of use of illicit drugs
    - History of newly-acquired syphilis, gonorrhoea, non-gonococcal urethritis, HSV-2, chlamydia, pelvic inflammatory disease (PID), trichomonas, mucopurulent cervicitis, epididymitis, proctitis, lymphogranuloma venereum, chancroid, or hepatitis B;
    - Three or more sexual partners
  5. If female, pregnant or planning a pregnancy within 4 months after last study vaccination; or lactating;
  6. Asthma requiring high-dose oral or inhaled corticosteroids;
  7. Bleeding disorder that was diagnosed by a physician (e.g., factor deficiency, coagulopathy or platelet disorder that requires special precautions) (Note: A volunteer who states that he or she has easy bruising or bleeding, but does not have a formal diagnosis and has IM injections and blood draws without any adverse experience, is eligible);
  8. History of splenectomy;
  9. Any of the following abnormal laboratory parameters listed below:
    - Haematology
      - Haemoglobin  $\leq 9.0$  g/dL **or**  $\leq 5.55$  mmol/L
      - Absolute Neutrophil Count (ANC):  $\leq 1000/\text{mm}^3$  **or**  $\leq 1.0 \times 10^9/\text{L}$
      - Absolute Lymphocyte Count (ALC):  $\leq 500/\text{mm}^3$  **or**  $\leq 0.5 \times 10^9/\text{L}$
      - Platelets:  $\leq 90,000 \geq 550,000/\text{mm}^3$  **or**  $\leq 90 \times 10^9 \geq 550 \times 10^9/\text{L}$
    - Chemistry
      - Creatinine:  $>1.4$  x upper limit of normal (ULN)

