#### Volunteer Information Sheet/ Informed Consent Document

A qualified member of the study staff will conduct the informed consent process by reviewing the Volunteer Information Sheet.

The following study-specific elements are included:

1. The vaccines tested in this study cannot cause HIV or AIDS.
2. If a vaccine recipient is exposed to HIV through exposure in the community and acquires HIV, it is not known whether the study vaccine(s) could increase, decrease or have no effect on: a) the risk of becoming infected with HIV; b) if infected, the course of HIV infection and; c) if infected, the time it takes to develop AIDS after being infected
3. The vaccine recipient may develop antibodies against HIV following vaccination, which is desirable but may produce a positive result in a routine HIV antibody test, and that provisions have been made to distinguish between response to vaccine and natural HIV infection during and after the study. In case the volunteer has a positive result due to vaccine-induced antibodies in a routine HIV antibody test, he/she will be followed until the result is no longer positive.
4. Women of childbearing potential should use a reliable non-barrier form of contraception from screening, during the vaccination period and until 4 months after the last vaccination
5. Placebo will be administered in this study and volunteer may receive placebo throughout the study

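### Inclusion 7b sets no condition on the partner's HIV status, so a monogamous volunteer with a known HIV-infected partner who reports condom use counts as low risk

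*Protocol*

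**What the plan says.** Section 5.2.2 describes the population as "healthy male or female adults aged 18-50 years at low risk for HIV infection", and section 3.1 also restricts the trial to low-risk adults.

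Section 5.2.3, item 7, makes this operational. Clinic staff assess low risk "on the basis of self-reported sexual behaviour within the 12 months prior to enrolment defined as follows", followed by a list joined by the word or:

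- 7a: sexual abstinence.
- 7b: "Had two or fewer mutually monogamous relationships with partners who did not use illicit drugs, or"
- 7c: "Had two or fewer partners believed to be HIV-uninfected and who did not use illicit drugs", together with regular condom use.

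Section 5.2.4, exclusion 4, lists reported risky behaviour in the 12 months before vaccination. Its first bullet is "Unprotected sexual intercourse with a known HIV-infected person, a partner known to be at high risk of HIV infection or a casual partner". The other bullets concern sex work, alcohol and drug use, recent sexually transmitted infection, and three or more partners.

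Inclusion 5 asks that the volunteer be "committed to maintaining low risk behaviour for the trial duration". Exclusion 26 lets the Principal Investigator exclude anyone for whom participation is not in their best interest.

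**The concern.** Mutual monogamy protects against HIV only if the partner is uninfected. Item 7b drops the condom condition of 7c but does not add the condition on the partner that would justify dropping it. That condition is written out in the next item of the same list, so its absence from 7b looks like an oversight.

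The definition matters for safety. The information given to volunteers (section 7.1) says that, for someone who is exposed and acquires HIV, "it is not known whether the study vaccine(s) could increase, decrease or have no effect on" the risk of infection and its course. Entry criteria also carry weight because HIV testing is sparse early on. In Groups 1-3 the first scheduled test after screening is on day 84, after the vaccinations on days 0, 28 and 56 (Appendix A).

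An intercurrent infection stops vaccination and leads to an early termination visit (sections 10.7 and 11.3.2), so later vaccinations or follow-up can be lost.

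**Working it through.** The protocol states no figure on this point and no formula applies. The check is to apply the criteria as a site would.

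**Step 1: how many items of the list are needed.** The items are alternatives, so a volunteer who meets 7b need not meet 7c. The partner-status and condom conditions of 7c bind only those who qualify through 7c.

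**Step 2: apply the criteria to two volunteers.** Both are mutually monogamous, each with a partner who does not use illicit drugs and is known to be HIV-infected.

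- *Condoms always used, by self-report.* 7a: not met. 7b: met. 7c: not met. Exclusion 4, first bullet: not triggered, because the intercourse was not unprotected. Exclusion 4, other bullets: not about partner status. Result: eligible, and low risk by definition.
- *Any unprotected intercourse in the past 12 months.* 7b: met. Exclusion 4, first bullet: triggered. Result: excluded.

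The gap is therefore confined to the first volunteer.

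**Step 3: check the other safeguards.** The staff assessment in item 7 is tied to the a/b/c list. Inclusion 5 gives no definition of low-risk behaviour of its own. The screening assessment and the HIV risk assessment (sections 9.3.5 and 9.3.6) may reveal an infected partner, but the protocol does not say that this makes a volunteer ineligible. Exclusion 26 is discretionary and not tied to partner status. Each may catch the volunteer; none requires it.

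**Step 4: what an infection would cost.** This follows from the appendices.

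- Groups 1-3: vaccinations on days 0, 28, 56 and 168; HIV tests after baseline on days 84, 196 and 336. An infection found on day 84 costs the day 168 vaccination. One found on day 196 comes 196 - 168 = 28 days after the last vaccination, with 336 - 196 = 140 days of follow-up remaining.
- Groups 4-5: vaccinations on days 0 and 112; tests on days 28, 140 and 336. An infection found on day 28 costs the day 112 vaccination. One found on day 140 comes 140 - 112 = 28 days after the last vaccination, with 336 - 140 = 196 days remaining.
- Day 336 is the final visit in all groups.

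The loss thus depends on when the infection is found.

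**Step 5: test the repair.** With 7c's qualifier in 7b, the first volunteer in step 2 fails 7a, 7b and 7c and is no longer low risk, whether or not exclusion 4 changes.

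**The case against.** The strongest reply is that the wording may be deliberate. The synopsis frames the population by behaviour, as people not reporting high-risk conduct. Exclusion 4 considers known infected partners expressly and limits the bar to unprotected sex, so the authors may have judged protected sex acceptable. This stands as a reason not to rewrite exclusion 4 on a reviewer's initiative. It does not explain why 7c, which already requires condoms, also demands a partner believed uninfected while 7b demands neither.

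It is also fair that exposure is residual, since any unprotected intercourse with a known infected partner within 12 months already excludes. That limits the size of the point and is accepted.

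A reader might infer more than the documents support:

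- *That a monogamous volunteer with an untested partner and no condoms shows a further defect.* This is ordinary monogamy, which 7b evidently means to accept. The qualifier in 7c is a belief, not a test result, so most such volunteers would qualify after the repair too.
- *That only exclusion 26 stands in the way.* Inclusion 5, the staff assessment and the risk assessments do as well, although none names partner status.
- *That every infection removes one twelfth of a vaccine group.* Of the 75 volunteers, 15 (20%) receive placebo, data already collected remain, and tests on days 196 and 140 fall 28 days after the last vaccination.
- *That a probability of infection can be attached.* The documents give neither an incidence nor the number of such volunteers, so any figure would be assumed on both counts.

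**Conclusion.** The inconsistency is real and narrow. Read literally, 7b and exclusion 4 together classify a monogamous volunteer with a known HIV-infected partner and reported condom use as low risk. This disagrees with 7c and with the population stated in sections 3.1 and 5.2.2.

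The conclusion rests on reading item 7 as true alternatives and on sites applying the list as written; a cautious site could still turn the volunteer away. That the low-risk restriction exists because of the unknown effect of the vaccines on HIV acquisition is a reasonable inference, but the protocol does not say so.

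The consequences are for volunteer safety and for possible loss of later vaccinations or follow-up after an intercurrent infection. No stated sample size, power or confidence limit is affected, and the frequency cannot be estimated from the document.

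**What to change.** Reconcile 7b with 7c by using in 7b the partner condition that 7c already contains ("Had two or fewer partners believed to be HIV-uninfected and who did not use illicit drugs"), so that the partners in a mutually monogamous relationship must also be believed HIV-uninfected. The condom condition of 7c need not be carried over.

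The sponsor should then confirm that exclusion 4 is consistent with the amended item 7. A new exclusion bullet is not needed, because the inclusion criterion would settle the case.

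The cost is one phrase in the protocol and a matching line on the form used to assess risk at screening. The downside is that a few volunteers in serodiscordant couples become ineligible.

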### 5.2.4 Exclusion Criteria

1. Confirmed HIV-1 or HIV-2 infection;
2. Any clinically relevant abnormality on history or examination including history of immunodeficiency or autoimmune disease; use of systemic corticosteroids (the use of topical or inhaled steroids is permitted); immunosuppressive, anti-cancer, anti-tuberculosis or other medications considered significant by the investigator within the previous 6 months;
3. Any clinically significant acute or chronic medical condition that is considered progressive, or in the opinion of the investigator, makes the volunteer unsuitable

- for participation in the study;
4. Reported risky behaviour for HIV infection within 12 months prior to vaccination, as defined by:
    - Unprotected sexual intercourse with a known HIV-infected person, a partner known to be at high risk of HIV infection or a casual partner (i.e., no continuing established relationship)
    - Engaged in sex work
    - Frequent excessive daily alcohol use or frequent binge drinking or chronic marijuana or any other use of use of illicit drugs
    - History of newly-acquired syphilis, gonorrhoea, non-gonococcal urethritis, HSV-2, chlamydia, pelvic inflammatory disease (PID), trichomonas, mucopurulent cervicitis, epididymitis, proctitis, lymphogranuloma venereum, chancroid, or hepatitis B;
    - Three or more sexual partners
  5. If female, pregnant or planning a pregnancy within 4 months after last study vaccination; or lactating;
  6. Asthma requiring high-dose oral or inhaled corticosteroids;
  7. Bleeding disorder that was diagnosed by a physician (e.g., factor deficiency, coagulopathy or platelet disorder that requires special precautions) (Note: A volunteer who states that he or she has easy bruising or bleeding, but does not have a formal diagnosis and has IM injections and blood draws without any adverse experience, is eligible);
  8. History of splenectomy;
  9. Any of the following abnormal laboratory parameters listed below:
    - Haematology
      - Haemoglobin  $\leq 9.0$  g/dL **or**  $\leq 5.55$  mmol/L
      - Absolute Neutrophil Count (ANC):  $\leq 1000/\text{mm}^3$  **or**  $\leq 1.0 \times 10^9/\text{L}$
      - Absolute Lymphocyte Count (ALC):  $\leq 500/\text{mm}^3$  **or**  $\leq 0.5 \times 10^9/\text{L}$
      - Platelets:  $\leq 90,000 \geq 550,000/\text{mm}^3$  **or**  $\leq 90 \times 10^9 \geq 550 \times 10^9/\text{L}$
    - Chemistry
      - Creatinine:  $>1.4$  x upper limit of normal (ULN)
      - AST:  $\geq 2.6$  x ULN
      - ALT:  $\geq 2.6$  x ULN
    - Urinalysis: clinically significant abnormal dipstick confirmed by microscopy
      - Protein 2+ or more
      - Blood 2+ or more (not due to menses);
  10. Receipt of live-attenuated vaccine within the previous 60 days or planned receipt within 60 days after vaccination with Investigational Product; or receipt of other vaccine, allergy treatment with antigen injections or tuberculin skin test within the previous 14 days or planned receipt within 14 days after vaccination with Investigational Product;
  11. Receipt of blood transfusion or blood-derived products within the previous 3 months;
  12. Participation in another clinical trial of an Investigational Product currently, within the previous 3 months or expected participation during this study;
  13. Prior receipt of another investigational HIV vaccine candidate (Note: receipt of

placebo in a previous HIV vaccine trial will not exclude a volunteer from participation if documentation is available and the Medical Monitor gives approval);

14. History of severe local or systemic reactogenicity to vaccines (e.g., anaphylaxis, respiratory difficulty, angioedema);
15. Positive for Hepatitis B surface antigen (HbsAg), positive for antibodies to Hepatitis C virus (HCV) or active syphilis;
16. Psychiatric condition that precludes compliance with the protocol. Specifically excluded are persons with psychoses within the past 3 years, ongoing risk for suicide, or history of suicide attempt or gesture within the past 3 years.
17. History of allergy or hypersensitivity to bupivacaine or any amide-type (local) anesthetics, such as lidocaine (Xylocaine®), mepivacaine (Polocaine®/Carbocaine®), etidocaine (Duranest®), bupivacaine (Marcaine®), or prilocaine or known hypersensitivity to any component of the products tested
18. History of allergy or hypersensitivity to latex
19. Chronic skin problems such as eczema or psoriasis
20. Presence of an implantable device [e.g. Automated Implantable Cardioverter-Defibrillator (AICD), pacemaker, {pain} medication administration pumps]
21. Current use of any electronic stimulation device, such as cardiac demand pacemakers, automatic implantable cardiac defibrillator, nerve stimulators, or deep brain stimulators.
22. History of, or known active cardiac disease or a heart condition under the care of a doctor, including cardiac arrhythmia [e.g., supraventricular tachycardia, atrial fibrillation, frequent ectopy, or sinus bradycardia (i.e., <50 beats per minute on exam)] prior to study entry. Note: Slight physiological variation of normal resting heart rate (60 - 100 beats/minute) with respiration is NOT excluded.
23. History of syncope or fainting episode within 1 year of study entry
24. Seizure disorder or any history of prior seizure
25. Skin and subcutaneous tissue thickness > 40 mm as assessed by skin pinch test in either deltoid region
26. If, in the opinion of the Principal Investigator, it is not in the best interest of the volunteer to participate in the trial

